| The SHINE study is a randomized controlled study of the effect of a park-based family support group on multiple outcomes (including stress and physical activity) in a low income population.   1. Primary hypothesis:   Children and caregivers enrolled in the SHINE program will have improved stress compared to those who are not enrolled in the SHINE program.   1. Secondary hypotheses:   Children and caregivers enrolled in the SHINE program will have improved social support, family functioning, physical activity, park visitation, and nature affinity compared to caregivers not enrolled in the program.  Children with obesity, ADHD, and asthma who participate in the SHINE program will show improvements in their symptoms.  The effect of the SHINE intervention will vary depending on the baseline life stressors present in the caregiver or child (the effects of nature interact with baseline stress and are dose dependent) and the dose of nature received.  During a SHINE outing, participants will experience immediate improvements in stress and 30 minutes of moderate-to-vigorous physical activity. | | | | | | | | | |  |
| **Purpose of the study:** What are the specific scientific aims of this study? | | | | | | | | | |  |
| Aim1: To determine changes in stress, social support, family function, physical activity, park visitation, and nature affinity amongst primary care patients ages 4 and older, and their caregivers enrolled in the SHINE intervention compared to those in a control group.Aim 2: To determine changes in BMI, ADHD symptoms, and asthma control for patients enrolled in the SHINE program compared to those who are not.Aim 3: To assess immediate changes in stress and minutes spent in moderate-to-vigorous physical activity by enrolled patients and their enrolled parents during SHINE outings. | | | | | | | | | |  |

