| To evaluate specific aims 1 and 2, the study design uses a randomized controlled trial design.  Potential participants will be given a short description of the study (Please see attached waiver to screen patients). If they agree to be screened, they will be screened for eligibility using a short screening tool.  If they are eligible based on the screening tool, they will consented and enrolled. All enrolled participants (which includes a caregiver and a child per family), will receive:   - Resources to find local parks - A recommendation to be physically active three times a week - A pedometer with a diary to record their daily steps - Three tubes for salivary cortisol collections   They will be asked to:   - Complete a questionnaire - Collect a first morning salivary cortisol during the first week, fourth week, and twelfth week of participation - Return to clinic to complete a questionnaire, and to have their child’s BMI measured, on the fourth week and twelfth week of participation - Turn in their physical activity logs on the fourth and twelfth week visits   Upon completing the baseline measures, participants will be randomized to one of two treatment groups ('A' or 'B') by a computer program (we will use Redcap) and the result recorded. Randomization will be blocked (using random permuted blocks) to ensure that the groups are balanced periodically.  The control group will have no added activities.  The intervention group will be asked to return to clinic on the first, second, and third week of the study at 1 pm - 4pm on Saturday. During these visits, they will meet with clinic staff as well as with other participating families. They will turn in their physical activity logs for a week. They will then board a school bus and travel to one of three local parks (Week 1 = Crab Cove, Week 2 = Temescal Lake, Week 3= Redwood Regional Park). Once at park, they will experience:   1. A warm welcome and ice breaker games 2. 30 minutes of lunch and unstructured play 3. 60 minutes of light walking   They will journal about their outdoor experiences. The journal will include questions about stress and well-being.  The intervention group will also be encouraged to visit a park or be physically active at least three times a week every week for six weeksand will be able to chronicle their outdoor physical activity in their journal.  To assess Aim 3 we will survey only the families in the intervention arm:  During the third SHINE outings, enrolled guardians and children will be invited to wear an accelerometer for the duration of the event. Accelerometers will be programmed to record data in 15-second intervals and will allow us to calculate minutes spent in moderate to vigorous physical activity. Participants will return their accelerometers prior to boarding the shuttles to return home. | | | | | | | | | |  |

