| We will examine differences in outcome variables between the guardians participating in the SHINE intervention and the control group and will stratify by age, If caregiver stress improves for participants in SHINE intervention decreases more than guardians in the control arm, we infer a functional relationship between the SHINE intervention and guardian stress.  We will present descriptive statistics of baseline covariates using means and proportions.  Our primary outcome (guardian stress) is measured by the PSS score, a continuous repeated measure. Because this study uses a randomized control design, we will use ANOVA procedures to estimate the effect of SHINE. We will also adjust for possible empirical confounding by incorporating covariates with a bivariable association with the primary outcome (guardian stress) into a multivariable ANOVA model.  Analyses will also explore potentional interaction that correspond to amount of pre-existing life stressors or ACE score, and nature exposure and the effect of SHINE on stress. We will estimate the degree to which measures of pre-existing stress account for the effects attributed to the particular SHINE.  .  Secondary outcomes of interest (child stress, BMI, ADHD score, asthma score) are also continuous measurements and will be analyzed using ANOVA procedures or other appropriate multivariable models accounting for correlations due to repeated measurements. We will also adjust for possible empirical confounding by incorporating covariates with a bivariable association with the secondary outcomes.  Aim 3. We will examine changes in stress, and minutes spent in moderate to vigorous physical activity duringhe SHINE intervention for participating guardians and children.  We will present changes in these continuous variables using a paired-t test.  Power Analysis  We calculated the power to detect differences of 0.5 effect size between the intervention and control group. With a type I error of 0.05, and a Type II error rate of 0.20, and a two-tailed statistical test.  Attrition and Missing Data  We expect 20% attrition among participants, and we do not expect participant attrition to vary by treatment condition - those receiving the intervention may have higher attrition than others. Both groups have the inconvenience of coming into clinic. One group has the extra time to spend, but it is also a bigger commitment. In light of attrition, however, we will attempt to identify key predictors of attrition status, such as [example predictors, e.g., SES, reading level], and test for differences between conditions. Our plan to deal with missing data is to analyze patients as intent to treat and will check for the impact of missing data using sensitivity analysis. |

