| Parental and child stress | Salivary cortisol | Participants will bring in early am cortisol | Baseline, 1 month, 3 months |
| Family Cohesion | FACES IV (Olson, 2011) | 7 item balanced cohesion scale taken by parents | Baseline, 1 month, 3 months |
| Connection to Nature | (Adults) Love and Care for Nature (Perkins, 2010) | 15 item self-report scale used to measure emotional connection to nature, tested for people 18 and older | Baseline, 1 month, 3 months |
|  | (Children) Connection to Nature Index (Bragg et al., 2013) | 16 item scale developed and tested for children aged 8-12 | Baseline, 1 month, 3 months |
| Physical Activity | Pedometry | Journals for use at home | Daily record for 6 weeks by participants in intervention arm |
|  | Accelerometry | Armbands placed during park outings | Week 3 outing |
| Increased Park Usage | One week recall self-report |  | Baseline, 1 month, 3 months |
| Obesity | BMI | Take their weight and height | Baseline, 1 month, 3 months |

Figure 1. Parent predictor and outcome variables

[figure not shown]

Figure 2. Child predictor and outcome variables

[figure not shown]

Supplement: S3 File — (DOCX) [file pone.0192921.s003.docx]

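### The dose-dependence hypothesis is examined as an interaction between SHINE and a nature dose that arises after randomisation, so an apparent dose effect can arise without a real one

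*Protocol*

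**What the plan says.** The secondary hypotheses (Protocol, Hypothesis) state that the SHINE effect will vary with baseline life stressors, since "the effects of nature interact with baseline stress and are dose dependent", "and the dose of nature received". So dose received is part of a stated hypothesis.

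The Statistical Analysis section says analyses will "explore potentional interaction that correspond to amount of pre-existing life stressors or ACE score, and nature exposure and the effect of SHINE on stress". Nature exposure is not defined there. It stands in one list with pre-existing stressors and the ACE score.

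Three other places matter:

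- **Timing.** Study Design states: "Upon completing the baseline measures, participants will be randomized to one of two treatment groups". The outings and independent visits come later.
- **Choice.** The SHINE arm is "encouraged to visit a park or be physically active at least three times a week" for six weeks. Three Saturday outings are scheduled, but attendance can vary.
- **Measurement.** Table 1 measures park use by "One week recall self-report" at baseline, 1 month and 3 months. SHINE families also keep a journal of their outdoor experiences and "will be able to chronicle their outdoor physical activity in their journal".

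Park visitation is also listed among the secondary outcomes that SHINE is expected to improve.

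**The concern.** An interaction test asks whether the effect of a randomised treatment differs between kinds of participant. It has that meaning when the characteristic is fixed before assignment, as life stressors and ACE score are if taken at baseline. Dose received is different. No dose level is assigned, families largely set it themselves, and SHINE is meant to raise it. Families with more time, easier transport, more motivation or less stress may go to parks more and also report less stress later. If that link is stronger in the SHINE arm than in the control arm, the interaction term will pick it up whatever nature exposure does.

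Measurement adds to the difficulty. The only park-use measure common to both arms is the one-week recall. Of its two post-randomisation readings, at 1 month and 3 months, at most one falls within the six-week programme.

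At stake is the interpretation of a named secondary hypothesis. The trial could report that nature works in a dose-dependent way when part or all of the pattern reflects who chose to go.

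**Working it through.** The plan gives no figure for this analysis, so there is nothing to reproduce. The question is how often the interaction test rejects when neither arm nor dose has any effect.

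**Inputs from the protocol.** 100 families, so about 50 guardians per arm (equal allocation assumed). Two-sided 5% level. Expected attrition 20%, so about 50 × 0.8 = 40 per arm at follow-up.

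**Assumed inputs.** The correlation between received dose and follow-up stress within each arm, arising only from shared causes: r0 in control, r1 in SHINE. The documents give neither, so a range is shown.

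**Formula.** With dose and stress standardised within arm, the expected interaction coefficient is r1 − r0. Its standard error is about √{[(1 − r1²) + (1 − r0²)]/n}, with n per arm. With z = |r1 − r0|/SE, the rejection rate is about Φ(z − 1.96) + Φ(−z − 1.96).

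For r0 = 0, r1 = −0.3 and n = 50: SE = √{(0.91 + 1)/50} = 0.195, z = 0.3/0.195 = 1.54, rate about 34%. Simulating the fitted model (stress on arm, dose and arm × dose) gives 32%.

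| r0 (control) | r1 (SHINE) | SE | z | Approximation | Simulated, 50 per arm |
|---|---|---|---|---|---|
| −0.3 | −0.3 | 0.191 | 0 | 5% | 5% |
| −0.2 | −0.3 | 0.193 | 0.52 | 8% | 8% |
| 0 | −0.2 | 0.198 | 1.01 | 17% | 17% |
| 0 | −0.3 | 0.195 | 1.54 | 34% | 32% |
| 0 | −0.4 | 0.192 | 2.09 | 55% | 53% |

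With 40 per arm the last two simulated rates fall to about 26% and 43%.

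**Second model.** A latent trait lowers stress with coefficient g and raises dose with coefficient r, giving a dose-stress correlation of −g × r. Dose has no effect on stress. With selection in the SHINE arm only and 50 per arm:

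- g = r = 0.3 (correlation −0.09): 6.9%
- g = r = 0.5 (−0.25): 23.7%
- g = 0.5, r = 0.7 (−0.35): 42.3%
- g = r = 0.7 (−0.49): 71.7%

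With g = 0.5 and r = 0.5 in SHINE but 0.25 in control, the rate is 10.3%. With equal selection (g = r = 0.5 in both arms) it is 4.9%. These agree with the table: what drives the false-positive rate is the difference in selection between arms. Results are about the same when a true arm effect of 0.5 SD is added.

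**Effect of using baseline stress.** A stable shared cause enters baseline and follow-up stress equally and cancels in the change score. For a within-arm slope with r = −0.3 and n = 50, the false-positive rate is about 57–58% on raw follow-up stress and about 5% on change from baseline. With baseline as a covariate it is 14–36%, for assumed baseline-to-follow-up correlations of 0.7 down to 0.3. Causes that change over time, and stress itself governing whether a family goes out, do not cancel.

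**The case against.** The best defence is that the analysis section only promises to explore, never defines nature exposure, and lists it beside characteristics fixed in advance. Table 1 collects park use at baseline, so exposure could mean baseline exposure. The figures of predictor and outcome variables are not visible in the text reviewed, and a separate analysis plan may define the variable. This tempers certainty about the exact model. It does not remove the point, because the hypothesis itself names dose received, and calling an analysis exploratory does not remove its bias.

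The second defence is about size, and much of it stands. Controls also receive park resources and activity advice, so they too choose their park visits. If selection is similar in both arms, the interaction test stays close to 5%. Aim 1 concerns change in stress, and the plan treats the stress score as a repeated measure and adjusts for associated covariates. A change-score analysis would remove bias from stable shared causes.

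Some stronger readings are tempting but not supported:

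- A reader might infer that most such trials would show a false dose response. At r = −0.2, −0.3 and −0.4, a slope fitted within a SHINE arm of 50 is falsely significant in about 29%, 58% and 84% of trials. The plan describes no such within-arm test, so those rates do not describe the planned interaction.
- A reader might infer that the whole SHINE journal is optional. The permissive wording covers only the outdoor physical activity entries. All participants also get a step diary, although steps do not measure nature exposure.
- A reader might infer that the main result is compromised. The randomised comparison of guardian stress does not use dose.

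**Conclusion.** The point holds as a limit on what the dose analysis can show. The protocol hypothesises dependence on dose received and examines nature exposure as an effect modifier. That dose is post-randomisation, largely self-selected and partly an outcome. The plan states no method suited to such a variable and no caution against a causal reading. Covariate adjustment cannot be relied on to remove unmeasured causes such as motivation, time or transport.

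The false-positive rate runs from the nominal 5% under equal selection to about 53% at 0 against −0.4 with 50 per arm, and is somewhat lower with 40. In the table, rates above 30% need correlations that differ by at least 0.3 between arms. Some difference is plausible, because only SHINE has the outings and six weeks of encouragement, but its size is an assumption. The rates also assume that stress is analysed without using its baseline value.

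**What to change.** In the secondary hypotheses and the Statistical Analysis section, limit interaction tests to variables fixed before randomisation: life stressors, ACE score, and baseline park use from the one-week recall in Table 1.

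Report any analysis of received dose only as a description within the SHINE arm, adjusted for baseline stress. Label it observational and do not use it to support dose dependence. The label is still needed after adjustment, as the residual rates above show. If outing attendance is the dose, state that it will be recorded, since neither Table 1 nor the procedures list it.

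Using assignment as an instrument for outings attended is not a ready substitute. SHINE families also journal and are encouraged to visit parks or be active for six weeks, so assignment may act by other routes. A single two-level instrument also cannot test dose-response. Leave it out, or state that it assumes assignment acts only through outings attended and that it does not test dose-response.

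The cost is wording, plus an attendance log if attendance is used. The downside is a weaker dose-dependence claim.

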| Our system for equitable selection of study patients is to use a screening tool that will ensure systematic enactment of our inclusion and exclusion criteria.Inclusion criteria are: the adult must be the legal guardian, at least 18 years old and familiar with the child’s health. The enrolled child must be at least 4 years old. This age cut-off for participating children was chosen because of programming considerations once the families are in the parks and in order to measure physical activity in the child. Because we are measuring physical activity, the caregiver and child need to have no physical disabilities that would limit their ability to be able to be physically active.  Both caregiver and child must be willing to be randomized, and must be available for follow up over the next 3 months. If they are randomized to the intervention group must return to clinic weeks 1, 2, 3 on Saturdays for group park visits, as well as to visit parks on their own for six weeks. | | | | | | | | | |  |
| 1. **Eligibility for Study:** How is eligibility determined and by whom? | | | | | | | | | |  |
| Eligibility for the study will be determined by the research coordinator by reading through the eligibility screen with referred patients and their guardians. All answers to the eligibility questions must be yes. If any of them are no, the patient will not be eligible. Any questions will be discussed with the study coordinator [name] or by the PI, [name]. | | | | | | | | | |  |
| 1. **Duration of Subjects' Participation in the Study (include follow-up if applicable):** | | | | | | | | | |  |
| Patients will be enrolled for a total of 12 weeks. They will participate in a survey at the time of randomization, at one month out from the beginning of the study, and three months after the end of the intervention. | | | | | | | | | |  |
| Enrollment Plan and Recruitment | | | | | | | | | |  |
| 1. **Planned Enrollment at CHRCO:**  Number of subjects needed to complete the study. | | | | | | | | 200 total participants (100 families with 1 adult and 1 child enrolled in each family) | |  |
| **Enrollment plan:** If you expect failed screenings or subject withdrawals, will they be replaced until the appropriate numbers of subjects have completed the study? If No, explain below. | | | | | | Yes XNo N/A | | | |  |

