| We need 200 participants (100 parent/child dyads) in order to complete this goal. In order to enroll this number, we anticipate screening 300 participants (150 parent/child dyads) for eligibility, enrolling 240 participants (120 parent/child dyads) and having 200 participants (100 parent/child dyads) participate in the programing.  If a subject fails a screening, we will keep record of their screening, and will continue screening until appropriate subjects have enrolled in the study.  Because our intervention arm has park outings that occur at a set time (either in July, August, or September), we may not be able to replace all subject withdrawals. We will have the option of increasing the number of participants in later sessions if the first session is under-enrolled. | | | | | | | | | |  |
| **Recruitment:** What methods will be used to identify and recruit potential subjects? Attach a copy of all planned advertisements, flyers and letters, etc. to potential subjects. | | | | | | | | | |  |
| Recruitment will occur through provider referral and self-referral. In order to advertise the study:We will present at staff meeting for health care providers. Potential participants referred by health care providers will be called by the research assistant.The research assistant will be present in the clinic waiting room during the first two weeks of each month.[name], the research coordinator or research assistant will approach patients who are waiting for their appointment, will describe the project, and ask their interest in being involved.Patients will be allowed to self-refer. A recruitment flier will be placed in the waiting room with the study coordinator’s phone number listed  - Patients will be given the opportunity to consent right there and then, or will have the opportunity to go home, consider, and call back later for screening/consent. | | | | | | | | | |  |
|  | Informed Consent | | | | | | | | |  |
|  | 1. **Capacity to Consent:** Will all subjects have the capacity to give informed consent? If not, describe the likely range of impairment and explain how, and by whom, their capacity to consent will be determined. | | | | | | | | |  |

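### The planned 100 families do not follow from the stated power inputs for guardian stress: a simple two-tailed comparison gives about 70% power, not 80%

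*Protocol*

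**What the plan says.** Under Data Analysis, Statistical Analysis, the protocol names the endpoint: "Our primary outcome (guardian stress) is measured by the PSS score, a continuous repeated measure". The Power Analysis paragraph in the same section reads "We calculated the power to detect differences of 0.5 effect size between the intervention and control group" and continues "With a type I error of 0.05, and a Type II error rate of 0.20, and a two-tailed statistical test". It gives no sample size, unit of analysis, allocation ratio or correlation.

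The sample size is under Enrollment Plan and Recruitment. Planned enrolment is "200 total participants (100 families with 1 adult and 1 child enrolled in each family", and the enrolment plan repeats it: "We need 200 participants (100 parent/child dyads) in order to complete this goal". The same paragraph foresees "enrolling 240 participants (120 parent/child dyads) and having 200 participants (100 parent/child dyads) participate in the programing". It adds that not every withdrawal can be replaced, because the outings run on fixed dates.

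The Attrition and Missing Data paragraph says "We expect 20% attrition among participants". The Study Design section describes two groups: "Randomization will be blocked (using random permuted blocks) to ensure that the groups are balanced periodically". Table 1 schedules the PSS-10 at baseline, 1 month and 3 months.

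**The concern.** The protocol fixes all the inputs of a standard two-group power calculation and, in another section, fixes the number of families. Each family supplies one guardian, so the primary comparison has as many independent units as there are families. The number of families required by the stated inputs is larger than the number planned.

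The stated chance of missing a true 0.5 SD effect on the primary outcome is 20%. In a simple comparison the planned numbers put it at 30% to 32%. Anyone who relies on the stated error rate to interpret a null result would give that result more weight than the design supports.

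A smaller inconsistency goes with it: the expected loss differs between the enrolment section and the attrition paragraph, so it is unclear how many guardians the power should refer to.

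**Working it through.** **Inputs.** Standardised difference d = 0.5, two-tailed alpha 0.05 and type II error 0.20 (Power Analysis); one guardian per family, 100 families needed, 120 enrolled (Enrollment Plan and Recruitment); 20% attrition (Attrition and Missing Data). Assumed, because the protocol does not say: 1:1 allocation, and an unadjusted comparison at one follow-up.

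**Step 1: number needed.** By the normal approximation, n per arm = 2(z₀.₉₇₅ + z₀.₈₀)² / d² = 2(1.960 + 0.842)² / 0.25 = 62.8, so 63 per arm or 126 families. The exact t-test calculation gives 63.8, so 64 per arm or 128 families. With 20% attrition this means enrolling 126/0.8 = 157.5, so 158, to 128/0.8 = 160 families. The planned 100 is not reproduced.

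**Step 2: power at the planned numbers.** Power ≈ Φ(d√(n/2) − 1.960). For n = 50 per arm: 0.5 × √25 = 2.5; 2.5 − 1.960 = 0.54; Φ(0.54) = 0.705.

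| Guardians analysed | Per arm | Normal | t-test |
|---|---|---|---|
| 120 (all enrolled, no loss) | 60 | 0.782 | 0.775 |
| 100 (number needed) | 50 | 0.705 | 0.697 |
| 96 (120 less 20%) | 48 | 0.688 | 0.679 |
| 80 (100 less 20%) | 40 | 0.609 | 0.598 |

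No count of guardians in the protocol reaches 0.80. The difference detectable with 80% power (t-test) is 0.566 SD with 50 per arm and 0.578 SD with 48 per arm.

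**Step 3: can the 100 be reproduced another way?**
- As 200 independent people, 100 per arm: power 0.94, not 0.80.
- With a one-sided 0.05 test: n = 2(1.645 + 0.842)² / 0.25 = 49.5, so 50 per arm, with power 0.804. This matches 100 families but contradicts the stated two-tailed test.

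**Step 4: effect of using the repeated measurements.** The protocol gives no correlation, so each figure here rests on an assumed one (normal approximation, two-tailed).
- Adjusting one follow-up for baseline multiplies the variance by 1 − r². With 50 per arm, power is 0.705, 0.746, 0.779, 0.823, 0.878 and 0.938 at r = 0, 0.3, 0.4, 0.5, 0.6 and 0.7. It reaches 0.80 at r of about 0.45. With 48 per arm it is 0.762 at r = 0.4 and 0.807 at r = 0.5 (about 0.80 by the t calculation).
- Averaging the two follow-ups without baseline, with the same effect at both, gives 0.873, 0.823, 0.798 and 0.774 with 50 per arm at between-visit correlations of 0.3, 0.5, 0.6 and 0.7.
- An unadjusted change score gives 0.42 at r = 0 and 0.90 at r = 0.7, so repeated measurement does not by itself raise power.

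**Step 5: attrition.** 1 − 100/120 = 16.7%. A 20% loss from 120 leaves 120 × 0.8 = 96. Keeping 100 after a 20% loss needs 100/0.8 = 125.

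**The case against.** The strongest objection is that the 70% figure depends on a simple analysis. PSS is measured three times and the protocol plans a covariate-adjusted model, so an efficient analysis could reach 80% with 100 or even 96 guardians. That stands, and the 70% must carry its label: unadjusted, one time point. It does not rescue the paragraph, which states no correlation and does not say that the power calculation used baseline adjustment or averaging. Step 4 shows that the result depends on both.

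A second objection is that the power paragraph never attaches its 80% to 100 families. This is also fair: the mismatch appears only when two sections are joined. But the enrolment section presents 100 dyads as the number needed, and the protocol offers no other number for the stated inputs. The point therefore concerns two statements that disagree, rather than detail that could be left to a statistical analysis plan.

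A reader might infer that the shortfall arose because caregivers and children were counted together as 200 units. The protocol does not support this. It equates 200 participants with 100 families or dyads each time, and 200 independent units would give 94%. A reader might also infer that a one-sided test was used, since it reproduces 100 families. That remains a guess, because the calculation is not shown and the text says two-tailed.

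On attrition, 120 is also 100 × 1.2, a common way of adding 20%, and taking part in the programme is not clearly the same as giving follow-up data. So the mismatch is real but secondary.

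**Conclusion.** The concern holds in this form: under the stated effect size, two-tailed alpha and type II error, the planned 100 families do not deliver 80% power in a simple comparison of guardian PSS. Power is about 70% with 50 per arm and about 68% with 48 per arm, against about 64 per arm required. The conclusion rests on 1:1 allocation, one guardian per family, and an unadjusted comparison at a single follow-up. It does not show that every reasonable analysis falls short: with baseline adjustment, 80% is attainable if the baseline-to-follow-up correlation is about 0.45 or more with 100 guardians, or about 0.5 with 96. No cause for the discrepancy can be asserted. The 16.7% and 20% losses should be reconciled in the same edit.

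**What to change.** Restate the Power Analysis paragraph per guardian, giving the number analysed, the allocation ratio, the sidedness and the analysis assumed. Use one attrition figure there, in the attrition paragraph and in the enrolment plan, and say whether 100 is a count before or after loss. Either of these would be consistent:

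- **Unadjusted, one time point:** 120 dyads randomised 1:1 with 20% attrition leave 96 guardians (48 per arm), giving about 68% power for 0.5 SD, or 80% power for about 0.58 SD, two-tailed 0.05.
- **Baseline-adjusted:** 96 guardians give about 80% power for 0.5 SD if the correlation between baseline and follow-up PSS is at least about 0.5. The analysis must be named as the basis of the calculation and the correlation labelled an assumption.

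The cost is a change of wording in the power, attrition and enrolment paragraphs. No additional participants are needed. Under the first option the stated power becomes less favourable; under the second it depends openly on an assumption that the protocol does not currently support with data.

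### The stated power inputs (effect size 0.5, two-tailed 5%, type II error 0.20) do not give the 100 families stated as needed; a simple comparison of 50 guardians per arm has about 70% power

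*Protocol*

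**What the plan says.** Under Data Analysis, Statistical Analysis, the Power Analysis paragraph reads "We calculated the power to detect differences of 0.5 effect size between the intervention and control group". It continues: "With a type I error of 0.05, and a Type II error rate of 0.20, and a two-tailed statistical test". The paragraph gives no resulting number of families or participants.

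The number is in Enrollment Plan and Recruitment. The planned-enrollment field, which asks how many subjects are needed to complete the study, gives 200 participants in 100 families of one adult and one child. The enrollment plan repeats it: "We need 200 participants (100 parent/child dyads) in order to complete this goal". It expects to get there by "enrolling 240 participants (120 parent/child dyads) and having 200 participants (100 parent/child dyads) participate in the programing".

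On the endpoint, the Statistical Analysis item says: "Our primary outcome (guardian stress) is measured by the PSS score, a continuous repeated measure". Table 1 schedules the PSS-10 at baseline, 1 month and 3 months. Under Study Design, "participants will be randomized to one of two treatment groups" in permuted blocks meant to keep the groups balanced; no allocation ratio is given. The Attrition paragraph expects 20% loss.

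**The concern.** The protocol gives an effect size, a two-sided error rate, a power and a number needed. For a two-group comparison these determine one another, and here they do not agree.

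The headline of 200 participants can hide this, because half of them are children and contribute nothing to guardian PSS. The primary comparison rests on one guardian per family, hence on 100 people.

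At stake is how a null result on guardian stress would be read. The plan tells readers that a true 0.5 SD effect would be missed 20% of the time. Under the plain reading of its figures the miss rate is about 30%, so a null result would be taken as stronger evidence against an effect of that size than it is.

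**Working it through.** **Inputs.** From the Power Analysis paragraph: effect size 0.5, alpha 0.05 two-tailed, power 1 − 0.20 = 0.80. From the enrollment section: 100 families needed, 120 enrolled. From the Attrition paragraph: 20% loss. Two assumptions are added: 0.5 is a standardised mean difference (no SD on the PSS scale is given), and allocation is 1:1. Unequal allocation would only lower power.

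**Number needed for the stated inputs.** By the normal formula, n per arm = 2(1.960 + 0.842)² / 0.5² = 62.8, so 63 per arm, or 126 guardians. The two-sample t test (noncentral t) gives 63.8, so 64 per arm, or 128 guardians. The stated 100 is not reproduced. With 20% attrition, 128 analysable guardians would mean enrolling 128 / 0.8 = 160 families.

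**Power at the plan's own counts** (t test, d = 0.5, two-tailed 5%, one visit, no baseline adjustment):

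| Guardians analysed | Per arm | Power |
|---|---|---|
| 120 (all enrolled, no loss) | 60 | 77.5% |
| 100 (the stated number needed) | 50 | 69.7% |
| 96 (120 × 0.8) | 48 | 67.9% |
| 80 (100 × 0.8) | 40 | 59.8% |

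The normal approximation gives 78.2%, 70.5%, 68.8% and 60.9% for the same rows.

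**Detectable difference.** With 50 per arm and 80% power, the t test gives 0.566 SD, about 0.57 (normal formula: 2.802 × √(2/50) = 0.560).

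**What repeated measurement could add.** The protocol states no correlation, so r below is an assumed range. All figures are for 50 analysed per arm.

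- *One follow-up adjusted for baseline.* The residual SD is multiplied by √(1 − r²). Power is 73.7% at r = 0.3, 77.1% at r = 0.4 and 81.6% at r = 0.5. It reaches 80% at about r = 0.47.
- *Unadjusted mean of the two follow-ups, same effect at both.* The SD is multiplied by √((1 + r)/2). Power is 86.7% at r = 0.3, 84.1% at r = 0.4, 81.6% at r = 0.5 and 79.0% at r = 0.6.
- *Change from baseline to one follow-up.* The SD is multiplied by √(2(1 − r)). At r = 0.5 this factor is 1, so power stays at 69.7%.

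These hold only if 50 per arm are analysed. At 48 per arm and r = 0.5, each of the first two gives 79.9%; at 40 per arm, 72.2%.

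**The case against.** The strongest reply is that the protocol does not say its test is a single-visit t test. It calls guardian PSS a repeated measure, schedules three assessments and plans ANOVA procedures. An analysis that uses the baseline or both follow-ups can reach 80% with 50 per arm, as shown above. This stands in part. A reader might infer from the 70% figure that no analysis of this trial's families could reach 80%, and the documents do not support that. But they do not show that such an analysis underlies the calculation either: neither a correlation nor a contrast is given for it, and a change score at r = 0.5 gains nothing.

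A second reply is that the power paragraph states no sample size, so the link to 100 families is inferred. That is true of the wording. But the form's item asks there how the sample size was determined, and the enrollment section gives 100 families as the number needed. Nothing else in the protocol supports that number. Nor can this be left wholly to an analysis plan that is not at hand, since the protocol itself states the inputs and the number that disagree.

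A reader might also infer that the size came from a one-tailed calculation, because a one-tailed 5% test with 50 per arm gives 79.9% power. The match is numerical only. The protocol says two-tailed, and nothing in it points to a one-tailed test.

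Counting all 200 participants as independent does not rescue the figure. It gives about 94%, which is not 80% either, and it does not fit a guardian-only outcome.

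**Conclusion.** The point holds in a limited form. As written, the stated power inputs do not give the stated number of families. For a two-group comparison of guardian PSS at one visit without baseline adjustment, they require 128 analysable families against the 100 given. With 100 families, power is 69.7% and the type II error about 0.30, against the stated 0.20. Enrolling 120 does not close the gap on this comparison, even with no loss.

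This rests on reading 0.5 as a standardised difference, on 1:1 allocation and on one guardian per family. The last is stated; the first two are assumed. It does not show that the planned repeated-measures analysis is underpowered. It shows that the 80% depends on assumptions the protocol has not stated.

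**What to change.** Restate the Power Analysis paragraph for the planned size, for example: *With 50 guardians per arm and two-tailed alpha 0.05, power for a 0.5 SD difference at one follow-up without baseline adjustment is about 70%; the difference detectable with 80% power is 0.57 SD.* Name the family (one guardian each) as the unit for the primary outcome, not the 200 participants, and state the allocation ratio and that the effect size is in SD units.

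If the sponsor prefers to keep 80%, the paragraph should state the contrast and correlation it relies on and derive the figure from them. At 50 analysed per arm, that means a baseline/follow-up correlation of about 0.47 or more for baseline adjustment at one follow-up. For the unadjusted mean of two follow-ups with equal effects, it means a correlation between them of up to about 0.5. The number analysed should allow for the stated 20% attrition.

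The cost is one paragraph of protocol text. The first option makes the stated power less favourable; neither option needs more families or a change of design.
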